### Participants

The eligibility criteria will be: Inclusion–(I) rearfoot striking runners with cadence under 170 steps/minute; (II) age between 18 and 45 years; (III) pain around or behind the patella, with intensity of at least 3/10 on the Visual Analogue Scale (VAS), during running and one task among squatting, climbing, and descending steps, kneeling and extending the knee with resistance [24]; (IV) being comfortable running at a speed of 10–12 km/hour. Exclusion—(I) Other disorders in the lower limbs; (II) history of surgery in the lower limbs in the last year; (III) not showing interest to adhere to a strict running retraining protocol for 2 weeks. Participants with unilateral or bilateral symptoms will be included, however, in the second case, only the worst knee (pain intensity) will be considered for analysis. The participants will be recruited through contact via e-mail, telephone, and through personnel with Goiânia’s running clubs in search of runners with PFP. In this first contact, general (gender, age, body mass, height, body mass index, history of injury and previous surgeries in the lower limbs), running (experience, volume, frequency) and pain information (intensity, location, duration of symptoms and functional tasks related to pain) will be assessed to see if the participants are eligible. Based on pain information, the diagnostic will be established using the following criteria: pain around or behind the patella during functional activities that loads the patellofemoral joint [24]. A systematic review of reviews concluded that anterior knee pain produced by functional tasks is currently the best diagnostic indicator of PFP [25]. Also, PFP is evident in 80% of the people who present anterior knee pain during a squatting manoeuvre [26].

Ethics approval was obtained from the Institutional Review Board of University of Brasilia/Faculty of Ceilândia (4.132.491), and all subjects will sign a detailed consent form before entering the study (S2–S4 Files). This study was registered in the Brazilian Registry of Clinical Trials (RBR-8yb47v) (S6 File).

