### Data collection

Pain will be assessed using the Visual Analog Pain Scale [29], which consists of a numerical scale from 0 to 10 points, where 0 means no pain and 10 means the maximum pain ever experienced. Pain during daily activities (usual) and running will be measured. VAS is a reliable and valid scale for patients with PFP [30]. Function will be assessed using the Patellofemoral Disorders Scale [31], which contains 13 questions that assess the severity of symptoms and limitations in different activities related to PFP. It presents a score between 0 to 100 points where the lower the score the worse the function. The Patellofemoral Disorders Scale is a reliable and valid scale for patients with PFP, which has been translated into Portuguese [30,31]. The kinematics of the lower limbs will be assessed through digital videos using two webcams (MyoVideo 139 HD Color Webcam) sampling at 30 frames per second and two leds (LED Floodlight) [32]. Reflective markers will be placed on the manubrium sterni and bilateral on the anterior superior iliac spine (ASIS), greater trochanter, lateral femoral epicondyle, fibular head and lateral malleolus [33]. All participants will be instructed to run at 10–12 km/hour on a motorized treadmill (Movement XL 1600). A treadmill acclimatization period of 6 min will be used before running kinematics are measured [34]. The frontal plane camera will be placed on a portable tripod perpendicular to the frontal plane at a height of 1.30m and a distance of 2.55m from the treadmill. The sagittal plane camera will be placed on a portable tripod, perpendicular to the sagittal plane at a height of 1.15m and a distance of 2.50m from the treadmill. The video recordings will be analyzed using the software MyoResearch 3.14—MyoVideo (Noraxon U.S.A. Inc.). In the frontal plane the angles assessed will be: contralateral pelvic drop; hip adduction [33,35,36]. These angles will be evaluated during midstance. In the sagittal plane the angles assessed will be: foot inclination; tibia inclination; ankle dorsiflexion; knee flexion [33,37,38]. Foot and tibia inclination will be evaluated during initial contact while ankle dorsiflexion and knee flexion during midstance. In the frontal plane, the deepest landing position (near midstance) will be determined visually by slowly advancing the video frame by frame [33,37,38]. Since the cameras are synchronized this position will also be used to determine the midstance in the sagittal plane. Initial contact will be determined visually by slowly advancing the video frame by frame, and will be defined as the first time that the foot touched the ground [37]. To analyze the proposed angles, seven steps will be considered [33]. The study of Dingenen and colleagues [39] has found excellent inter-rater reliability (ICC) for all angles with ICC’s ranging from 0.93 to 0.99.

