### Data analysis

The data of each participant will be extracted for SPSS (Statistical Package for Social Sciences) version 23.0 for later statistical analysis. Descriptive analysis will be performed with calculation of means, standard deviations and 95% confidence intervals for quantitative variables and frequencies and percentages for qualitative variables. Data normality and sphericity will be tested using the Shapiro-Wilk and Mauchly’s tests, respectively. Baseline demographic data will be compared using ANOVA (parametric data), Kruskall-Wallis (non-parametric data) and Chi-squared tests. To compare the effects of the rehabilitation programs on the outcomes of the study, a repeated measures ANOVA with a 3-by-3 mixed-model (parametric data) or the Generalized Estimation Equations procedure with gamma distribution model (non-parametric data) will be used. Time (t0 x t2 x t24) will be used as repeated factor, group (impact x cadence x control) as independent factor and the mean of points on the visual analog pain scale, mean of points on the Patellofemoral Disorders Scale, and the peak in degrees of the contralateral pelvic drop, hip adduction, ankle dorsiflexion and knee flexion during midstance, and foot inclination and tibia inclination during initial contact as dependent variables. Baseline characteristics that are different across groups will be included as covariates in the model. Significance level of p <0.05 will be adopted. Sidak’s post-hoc will be used to make pairwise comparisons. Subgroup analysis and adjusted analysis will not be performed. Intention-to-treat analyses will be conducted where the subjects will be analyzed independently of adherence to the protocol or retention in the follow-up.

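### The gamma GEE named for non-normal outcomes does not cover a pain score of 0, and at 7 to 10 runners per arm its usual robust group-by-time test would be too liberal

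*Protocol article*

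**What the plan says.** The Data analysis section gives every outcome one of two models. The default is a 3-by-3 repeated measures ANOVA. For data that are not normal, "the Generalized Estimation Equations procedure with gamma distribution model (non-parametric data) will be used". The choice rests on a test: "Data normality and sphericity will be tested using the Shapiro-Wilk and Mauchly’s tests, respectively". The analysis is to be run in SPSS 23.0, by intention to treat, with Sidak-adjusted pairwise comparisons at the 0.05 level.

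The Data collection section defines the pain measure as "a numerical scale from 0 to 10 points, where 0 means no pain". The Participants section requires pain "with intensity of at least 3/10 on the Visual Analogue Scale (VAS), during running and one task"; it sets no minimum for usual daily pain. The Outcomes measures section makes usual daily pain the primary outcome, while the Abstract names running pain. Both are scored on the same 0 to 10 scale, so the point below applies whichever is primary.

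The Sample size section gives 21 participants before losses and 30 in total.

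**The concern.** The article fixes a distribution that has no probability at a valid value of its main outcome. A score of 0 is also not a rare accident: it is complete relief, which is what the trial hopes to see at two weeks and six months. Usual daily pain may be 0 even at baseline. Scores piling up at 0 are also what makes a normality test fail, so the better the treatment works, the more likely the plan is to choose the model that does not fit.

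Two things are at stake. If zeros are excluded, the best results leave the pain analysis, chiefly in the arms that work. The estimated benefit is then understated, and records are selected by outcome, which conflicts with the stated intention-to-treat analysis. Separately, the robust variance normally used with GEE relies on many participants, and there are few here, so p-values may be too small.

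**Working it through.** **Inputs from the article.** Pain scale 0 to 10; three arms at 1:1:1; three visits; alpha 0.05; N = 21 before losses and 30 in total. That is 21/3 = 7 and 30/3 = 10 per arm.

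**The article's own figure.** f = √(0.19/0.81) = 0.484, stated as 0.48. Assume a correlation of 0.5 and no sphericity correction (neither is stated). The noncentrality is then f²·N·m/(1−ρ) = 0.48² × 21 × 3/0.5 = 29.0 on (3−1)(3−1) = 4 and (21−3)(3−1) = 36 degrees of freedom, which gives power 0.990. The 21 reproduces and is not in dispute. It serves here only to set the arm sizes.

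**Does gamma cover 0?** No. With shape 2, the log-density at 0 is minus infinity. The deviance term log(y/μ) is also minus infinity at y = 0. A zero therefore has no usable gamma likelihood.

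**Would the fallback be used?** One post-treatment visit was simulated with 10 per arm (assumed: rounded normal scores limited to 0-10, SD 2, control mean 4). With 16%, 23%, 31% and 41% zeros in the retraining arms, Shapiro-Wilk rejected in at least one arm in 37%, 51%, 70% and 88% of trials.

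**What excluding zeros does.** If a share p of an arm's scores is 0 and the positive scores average m, deletion raises the arm mean from (1−p)m to m, that is by p·m. The between-arm difference therefore moves toward zero by p_T·m_T − p_C·m_C. Simulated under the same type of assumption (SD 2):

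| Zeros, treated / control | Difference, all scores | Difference, zeros removed | Loss |
|---|---|---|---|
| 11% / 2% | −1.45 | −1.20 | 0.25 |
| 23% / 4% | −1.86 | −1.39 | 0.47 |
| 31% / 4% | −2.26 | −1.64 | 0.62 |
| 40% / 4% | −2.62 | −1.86 | 0.76 |

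**Type I error with few participants.** All rows have no true group effect. GEE rows use a gamma log-link model and, unless marked otherwise, the uncorrected sandwich variance with a chi-square reference.

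| Test, nominal 5% | 10 per arm | 7 per arm |
|---|---|---|
| Group-by-time, 4 df; gamma data, shape 2-10, correlation 0.3-0.6 | 16-21% | 24-29% |
| Group-by-time; gamma data, means 5/4/3.5 | 18.3% | 25.7% |
| Group-by-time; normal data limited to 0.1-10, means 5/4/3.5 | 13.7% | 19.1% |
| Group-by-time; rounded 0-10 scores, zeros kept | 14% | 18% |
| One between-arm contrast, unadjusted | 7.4-9.1% | 8.7-10.8% |
| Any Sidak-significant pair at t2, zeros kept | 7.4% | 9.4-9.6% |
| Group-by-time; bias-reduced variance, chi-square | 12.8% | 11.7% |
| Group-by-time; bias-reduced variance, F reference | 8.3% | 4.7% |
| Repeated measures ANOVA interaction | 5.2% | 3.8% |

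The last three rows use 600 runs, so a true 5% carries a Monte Carlo standard error of √(0.05 × 0.95/600) = 0.9 points. At 50 per arm the uncorrected group-by-time test falls to about 7-8%, which shows that the excess is mainly a small-sample effect.

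**The case against.** Several objections are sound and limit the point.

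- **Zeros need not be lost.** GEE solves quasi-score equations that require a positive mean, not positive observations. A gamma log-link GEE with an independence working correlation, fitted to simulated pain data containing 6 zeros, ran and returned cell means equal to the raw means. The article does not say how SPSS 23.0 treats zeros, so the deletion bias is conditional. What remains is that the named distribution does not describe valid data.
- **A reader might infer that pain-free participants would be dropped.** The documents do not support that. Any deletion in a GEE acts on visit records, and the entry rule of at least 3/10 during running means every participant keeps a baseline running-pain record.
- **A reader might infer that joint angles fail in the same way.** No sign convention is given for them, so zero or negative angles cannot be shown from the article, and the point does not rely on them.
- **The variance estimator, link and working correlation are not stated**, and an analysis plan may hold them. The inflation figures assume the usual uncorrected sandwich. They are large only for the 4-df group-by-time test; for the Sidak comparisons the excess is modest.
- **The two effects pull in opposite directions**, one hiding benefit and the other producing false positives. Their combined effect was not calculated.

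The answer that such details can wait for an analysis plan does not dispose of the point: the article itself already fixes both the distribution and the trigger.

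**Conclusion.** The fallback is wrong as written for the pain outcomes, because 0 is a valid and hoped-for score outside the range of a gamma distribution. If the software excludes non-positive values, the pain difference is biased toward zero by about 0.5 to 0.75 points, given 23-40% zeros in a treated arm and 4% in control. The true share of zeros is unknown, and fewer zeros mean less bias. If an uncorrected sandwich variance is used, the nominal 5% group-by-time test rejects about 14-29% of the time under no effect with 7 to 10 per arm, and Sidak pairwise testing at one visit about 7-10%.

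This should be fixed, but it is not fatal. It arises only if the fallback is triggered, and the default ANOVA kept close to its nominal level in the same simulations. A reader might go further and say that the trial's pain p-values will be wrong or its benefit certainly understated; the article does not state enough about software behaviour or variance estimation to support that.

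**What to change.** Before the data are analysed, amend the Data analysis section as follows.

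- Remove the gamma distribution for the two pain outcomes and state that all scores of 0 are kept.
- Use one mean-difference model for every outcome, whatever the normality test shows: a linear mixed model with small-sample degrees of freedom, or a GEE with normal distribution, identity link and small-sample-corrected variance. If GEE is kept, specify an F reference as well, since in the gamma GEE simulations the corrected variance with a chi-square reference still rejected about 12-13% of the time.
- If residuals are clearly non-normal, keep the same mean difference and take its p-value or interval from a permutation test or a bootstrap of whole participants stratified by group. With n per arm, a plain bootstrap understates the standard error of a mean by a factor of √((n−1)/n), which is 0.93 at 7 and 0.95 at 10, so permutation is the safer source for the p-value.

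This also keeps all outcomes on one scale, as mean differences. The linear mixed model is one acceptable choice among several; the essential parts are that zeros stay in and that the variance suits the sample size. The cost is revised wording and a little extra programming, with no change to recruitment, visits or data collection.

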### Sample size

An a priori sample size calculation was conducted using the eta-partial square value of the group-by-time interaction for worst knee pain (0.19) obtained in a previous study that compared the effects of three gait retraining programs on runners with patellofemoral pain [27]. In G*Power software [28], we used ANOVA: repeated measures, within-between interaction, with the following parameters: effect size f = 0.48 (obtained through eta-partial square value); level of confidence = 0.05; power = 99%; number of groups = 3; number of measurements = 3. The total sample size obtained was 21 participants, however, to account for losses during the follow-up period, the final sample size will be 30 participants.

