### Outcomes measures (dependent variables)

The primary outcome of the study will be: (I) pain during daily activities (usual)—assessed using the Visual Analog Pain Scale [29]; The secondary outcomes will be: (II) pain during running—assessed using the Visual Analog Pain Scale [29]; (III) function—assessed using the Patellofemoral Disorders Scale [31]; (IV) kinematics of the lower limbs in the frontal (contralateral pelvic drop; hip adduction) [33,35,36] and sagittal planes (foot inclination; tibia inclination; ankle dorsiflexion; knee flexion) [33,37,38]–assessed through digital videos using two webcams (MyoVideo 139 HD Color Webcam) sampling at 30 frames per second and two leds (LED Floodlight) [33]. The video recordings will be analyzed using the MyoResearch 3.14 –MyoVideo software (Noraxon U.S.A. Inc.). The kinematic variables of interest were chosen based on previous studies [14,15,19,47,48]. The systematic review and meta-analysis of Neal and colleagues [14] shows a relationship between increased hip adduction and contralateral pelvic drop with PFP. The study of Wille and colleagues [47] showed that foot inclination angle and peak of knee flexion are variables that may predict knee joint loading and PFJ forces during running. Tibia inclination during initial contact is related with cadence and length [48] and these are associated with PFJ forces [18,19]. For the comparison of the three study subgroups, the average of points on the visual analog scale of pain, average of points on the scale of Patellofemoral disorders and the peak in degrees of the contralateral pelvic drop, hip adduction, knee flexion and ankle dorsiflexion during midstance and foot inclination and tibia inclination during the initial contact will be considered. The three groups will be compared before (t0), immediately after (t2) and six months (t24) after starting the protocol.

Regarding the retention of the participants, to ensure that there are minimal losses during the follow-up period, the researchers will make a monthly phone call to monitor pain, the current level of training, physical activity practice and if the participants sought for other methods of treatment. Participants can withdraw from the study for any reason at any time, in which case the researchers will collect the pain and function outcomes using the aforementioned instruments (if possible) and report the reasons why these patients did not complete the follow-up (Fig 1).

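### The model uses each outcome's t0 value as a third time level with free arm means and not as a prespecified covariate, so the valid group comparison is less precise than the data allow

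*Protocol article*

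**What the plan says.** Data analysis sets out a 3-by-3 mixed-model ANOVA, or a gamma GEE for non-parametric data. One sentence defines the factors for both: "Time (t0 x t2 x t24) will be used as repeated factor, group (impact x cadence x control) as independent factor". Outcomes measures repeats the layout: "The three groups will be compared before (t0), immediately after (t2) and six months (t24) after starting the protocol". Sample size rests on the same structure, "ANOVA: repeated measures, within-between interaction, with the following parameters: effect size f = 0.48", with three measurements, so t0 counts as one of them.

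Two further sentences in Data analysis bear on covariates. One admits baseline characteristics as covariates only if they are found to differ between groups. The other rules out adjusted analysis. Neither makes the t0 value of an outcome a planned covariate. Pairwise comparisons use Sidak's method, but the contrasts to be tested are not specified.

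**The concern.** The arms are randomised, so their expected t0 values are equal and t0 carries no treatment effect. A model that estimates a separate t0 mean in each arm ignores this. Its group-by-time contrasts subtract the observed t0 difference in full, although only the part that predicts follow-up is useful. The rest is noise. The group main effect is also diluted, because it averages in a visit at which no effect can exist.

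The arms are small: 30 runners give 10 per arm, and the calculated 21 give 7. With 10 per arm, the difference between two arm means at t0 has SD √(2/10) = 0.447 in units of the outcome SD. A chance gap of at least 0.5 SD then occurs about 26% of the time. At stake is precision: a retraining effect could be missed that the same data would show after adjustment for t0.

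**Working it through.** **Inputs from Sample size.** The source effect is the "eta-partial square value of the group-by-time interaction for worst knee pain (0.19"), giving f = √(0.19/0.81) = 0.484, stated as 0.48. The other settings are "level of confidence = 0.05; power = 99%; number of groups = 3; number of measurements = 3". The result is N = 21, raised to 30 for losses.

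**Assumptions, not in the protocol.** Correlation rho between any two visits (0.3 to 0.8 examined); equal SDs across visits unless stated; both programs sharing one lasting effect, as the protocol hypothesises.

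**1. The plan's own figure.** For the within-between interaction, λ = f²·N·3/(1−rho), with 4 and 2(N−3) degrees of freedom. The settings do not include rho. With rho = 0.5 and sphericity:
- N = 21: λ = 0.2304 × 63/0.5 = 29.0, power 99.0% (99.1% with the unrounded f).
- N = 18: power 97.3%.
- N = 30: λ = 41.5, power 99.97%.

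So 21 reproduces at rho = 0.5. Other values of rho give other totals: 42 at rho 0, 30 at 0.3 and 15 at 0.7.

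**2. Variance of a pairwise contrast at t2** (per-runner scale, SD = 1). Change from t0: 2(1−rho). Adjusted for t0: 1−rho². The ratio is (1+rho)/2, below 1 for every rho below 1.

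| rho | change | t0-adjusted | reduction |
|---|---|---|---|
| 0.3 | 1.40 | 0.91 | 35% |
| 0.5 | 1.00 | 0.75 | 25% |
| 0.7 | 0.60 | 0.51 | 15% |

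**3. Pairwise power, 10 per arm.** Noncentral t with error pooled over three arms. The adjusted analysis pays one degree of freedom and a small penalty for estimating the slope. The Sidak level for three pairs is 1 − 0.95^(1/3) = 0.01695. True difference 1.0 SD:

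| rho | change, 0.05 | adjusted, 0.05 | change, Sidak | adjusted, Sidak |
|---|---|---|---|---|
| 0.3 | 44.5% | 60.0% | 27.5% | 41.5% |
| 0.5 | 57.8% | 68.4% | 39.4% | 50.2% |
| 0.7 | 79.5% | 84.0% | 63.5% | 69.6% |

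Over rho 0.3–0.8 and differences of 0.5–2.0 SD, the loss runs from 0 to about 19 points. With 7 per arm, rho 0.5 and 1.0 SD, it is 8.2 points (6.7 at Sidak).

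**4. At the plan's own effect.** If both programs share one lasting effect d, then f = d × 2/9, so d = 0.48 × 9/2 = 2.16 SD. At rho 0.5 and 10 per arm, pairwise power is 99.6% against about 100% (0.3 points), or 98.5% against 99.7% at Sidak (1.2 points). The omnibus test is already at 99.97%.

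**5. Another reading of 0.19.** If the published partial eta squared already contains the within-subject correlation (an assumption), λ = (0.19/0.81) × (30−3) × 2 = 12.67 at N = 30, and interaction power is 79%. At rho 0.5 this implies d = 1.19 SD. The pairwise loss is then 9.9 points (12.4 at Sidak). In simulation, a joint 4-df test on t2 and t24 given t0 reached 89% against 79% for the planned interaction (96% against 79% at rho 0.3; 83% against 79% at rho 0.7).

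**6. Unequal SDs.** With baseline SD s0 and follow-up SD s1, a change score has excess variance (s0 − rho·s1)² over the adjusted contrast.
- s0 = 0.7·s1, rho 0.5: change 0.49 + 1 − 0.70 = 0.79 against 0.75, a 5% reduction.
- s0 = 0.7·s1, rho 0.7: 0.49 + 1 − 0.98 = 0.51 against 0.51, no reduction.
- s0 = 1.3·s1, rho 0.5: 1.69 + 1 − 1.30 = 1.39 against 0.75, a 46% reduction.

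**The case against.** The strongest reply is that nothing here is invalid. The group-by-time test holds its error rate under randomisation and matches the model used for sample size. A reader might infer bias from chance differences at t0; the documents do not support that, since allocation is randomised. This part of the reply stands: the point concerns efficiency.

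A reader might also infer a definite loss of about 10 power points. That stands no better. It needs rho near 0.5, equal SDs and a true difference near 1 SD, and the protocol gives none of these. On its literal settings the omnibus test has almost nothing to gain. Entry requires running pain of at least 3/10, which may narrow the baseline SD of that outcome and shrink the gain; a floor at follow-up would enlarge it.

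Nor is it wrong in itself to keep t0 as a response. A longitudinal model with one common t0 mean for all arms does so and has essentially the efficiency of covariate adjustment. The loss comes from leaving the t0 means free.

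Finally, the Sidak comparisons are not stated to be raw contrasts at t2 or t24, so one cannot say that they ignore starting level. The diluted main effect is secondary, because the trial is sized on the interaction.

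What survives is that the article fixes the role of t0 outright, prespecifies no adjustment for it, and so gives up precision at no saving.

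**Conclusion.** The point holds as an avoidable loss of precision in a valid analysis. Adjusting for t0 never gives a larger contrast variance, apart from the degrees of freedom spent. With equal SDs the reduction is 35%, 25% or 15% at rho 0.3, 0.5 or 0.7. The pairwise power loss is conditional, from about 0 to 19 points under equal SDs with 10 per arm. It is about 10 near rho 0.5 and 1 SD, and near zero for the omnibus test if the plan's f = 0.48 and 99% power are taken literally. A somewhat narrower baseline SD makes it smaller and a wider one larger. These figures do not show that the trial is biased or that it must lose a set amount of power. The change is worth making because the t0 values are collected anyway.

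**What to change.** In Data analysis, for every outcome and in both the ANOVA and GEE branches, model t2 and t24 as the responses. Include the outcome's own t0 value and its interaction with time as prespecified covariates for all participants, whether or not the arms differ at baseline, plus group, time and group-by-time. Equivalently, keep t0 as a response but constrain it to a common mean across arms; this also keeps participants who have only t0 data.

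Name the t0-adjusted group differences at t2 and at t24, with 95% confidence intervals and Sidak adjustment, as the treatment test. The group-by-time term over t2 and t24 alone must not serve as that test: if the effect persists unchanged, as hypothesised, that term is zero and has no power.

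Reconcile the sentence that rules out adjusted analysis, and the one that admits covariates only when groups differ, with this wording.

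The cost is one or two residual degrees of freedom and a model that no longer exactly matches the G*Power description in Sample size. No new data, visits, participants or software are needed.

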
Unfortunately, the main gait retraining protocols are not feasible in clinical practice, since they consume a lot of time and financial resources for patients [11,23]. In fact, a recent study showed positive effects after a single session of cadence retraining on symptoms and biomechanics of runners with PFP [16]. Therefore, we chose to compare two partially supervised running retraining programs, one group focusing on impact and another group focusing on cadence.

The primary objective of the study will be to compare the effects of two different two-week partially supervised gait retraining programs, one focusing on impact and the other focusing on cadence, with a control intervention; on pain, function and lower limb kinematics of runners with PFP. The secondary objective of the study will be to compare the effects of these programs on pain, function and lower limb kinematics six months after their application.

Gait retraining with focus on impact has been proved to modify the ground reaction forces in pain free-subjects (tibial acceleration, vertical impact peak, instantaneous and average loading rates) [20–22], while the gait retraining with focus on cadence has been proved to modify symptoms, kinematic (increased hip adduction, contralateral pelvic drop and knee flexion) and kinetic aspects (patellofemoral loading rate) in patellofemoral pain patients [15,16]. Our hypothesis is that the two partially supervised gait retraining programs will be more effective in reducing pain, improving symptoms, and modifying lower limb kinematics during running compared with the control group, and that the positive effects from these programs will persist for six months. It is expected a reduction in contralateral pelvic drop, hip adduction, knee flexion, ankle dorsiflexion, tibia and foot inclination in both retraining groups. Also, we believe that one gait retraining group will not be superior to the other. The main motivations to perform a comparison of partially supervised gait retraining programs are the lack of clinical trials and the possibility to provide viable options for runners with PFP.

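### The primary question is each program against control, but the trial is powered on, and analysed first by, a three-group, three-time interaction, and no contrast or time point is named as decisive

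*Protocol article*

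**What the plan says.** The Introduction sets the primary objective as a comparison of two programs, described as "one focusing on impact and the other focusing on cadence, with a control intervention; on pain, function and lower limb kinematics of runners with PFP". A separate sentence begins "The secondary objective of the study will be to compare the effects of these programs" and places that comparison six months after the programs. The hypothesis is that both programs "will be more effective in reducing pain, improving symptoms, and modifying lower limb kinematics during running compared with the control group". The authors add a belief about the two programs: "we believe that one gait retraining group will not be superior to the other".

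The Sample size section powers "ANOVA: repeated measures, within-between interaction", with three groups, three measurements, f = 0.48, a 0.05 level and 99% power. This gives 21 participants, raised to 30 for losses.

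The Data analysis section uses the same structure: "Time (t0 x t2 x t24) will be used as repeated factor, group (impact x cadence x control) as independent factor". This is a 3-by-3 repeated-measures ANOVA, or a gamma GEE for non-parametric data. Sidak's "post-hoc will be used to make pairwise comparisons". No pair, time point or decision rule is singled out. The Outcomes section says only that the three groups will be compared at t0, t2 and t24.

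**The concern.** The objectives rank the questions: program against control comes first, and its persistence at six months second. The analysis does not carry that ranking over. The group-by-time interaction has (3-1)(3-1) = 4 degrees of freedom, treats t0 as one of the outcome levels, and responds to any departure from parallel profiles.

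Two things are at stake. First, a significant interaction could be read as confirming the primary hypothesis when the difference arose only at six months or only between the two programs. Secondly, a reader will take the 99% power as the chance of detecting a benefit over control, although it was calculated for another test.

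**Working it through.** **1. Reproduce the plan's figure.** f = sqrt(0.19/0.81) = 0.484, stated as 0.48. The correlation between repeated measures and the sphericity correction are not stated; I assume 0.5 and 1. Then lambda = f² × N × m/(1 - rho) = 0.2304 × 21 × 3/0.5 = 29.03, with df 4 and (21 - 3) × 2 = 36, and power is 0.990. The stated N of 21 is reproduced. The smallest N for 99% power would be 29 at correlation 0.3 and 14 at 0.7, so 0.5 is the value that fits.

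**2. What a significant interaction shows.** Let both programs differ from control by d (in SD units) at t2 only. The squared group deviations sum to (2/3)d². The squared deviations of the time pattern (0, 1, 0) sum to 2/3. So lambda = n × (4/9)d²/(1 - rho), with n per arm. The time patterns (0, 0, 1) and (0, 1, 1) also sum to 2/3, and one program differing from the other two arms again gives (2/3)d². All these cases have the same lambda and the same power, 0.990 at N = 21. The test cannot tell an effect at t2 from one at six months.

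**3. Power of the contrast at the protocol's effect size.** Setting 7 × (4/9)d²/0.5 = 29.03 gives d = 2.16 SD. At correlation 0.5 the SD of change, sqrt(2 × 0.5) = 1, equals the raw SD. The noncentrality is 2.16/sqrt(2/7) = 4.04 with 18 df. The Sidak levels are 1 - 0.95^(1/3) = 0.01695 over three pairs and 1 - 0.95^(1/2) = 0.02532 over two.

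| Per arm | Interaction | One contrast, Sidak over 3 | Sidak over 2 | Sidak over 2, baseline-adjusted |
|---|---|---|---|---|
| 7 | 0.990 | 0.907 | 0.935 | 0.981 |
| 10 | 1.000 | 0.985 | 0.991 | 0.999 |

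Here, dropping the program-against-program pair gains 2.8 points at 7 per arm and 0.6 at 10.

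**4. A smaller effect (assumed).** Take a 2-point benefit and SD 2, so d = 1, with 10 per arm. The change-score SD is 2 × sqrt(2(1 - rho)), with 27 df. The baseline-adjusted SD is 2 × sqrt(1 - rho²), with 26 df.

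| Contrast against control at t2 | rho 0.5 | rho 0.7 |
|---|---|---|
| Change score, Sidak over 3 | 0.394 | 0.635 |
| Change score, Sidak over 2 | 0.459 | 0.697 |
| Baseline-adjusted, Sidak over 3 | 0.521 | 0.716 |
| Baseline-adjusted, Sidak over 2 | 0.587 | 0.771 |

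At correlation 0.5, baseline adjustment alone adds 12.7 points and dropping the third pair alone adds 6.5. With 7 per arm the first and last rows become 0.254 and 0.407. At d = 0.8, 10 per arm and correlation 0.5 they become 0.244 and 0.394.

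**The case against.** The strongest reply is that the plan does reach the primary question. With three groups, Sidak pairs necessarily include each program against control, and the Outcomes section has the groups compared at t2. A reader might infer that the analysis cannot answer the objective. The documents do not support that; it is true only of the interaction taken alone.

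A reader might also infer that the plan wastes power on needless comparisons. That is not supported either. The program-against-program pair follows from a stated belief, and its multiplicity cost is modest. Most of the gain in step 4 comes from baseline adjustment, which is a separate choice. For the same d, the interaction has more power than a single adjusted contrast: 0.614 against 0.394 in step 4 at correlation 0.5.

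Two further limits stand. The primary objective does not state t2; there the two weeks describe the programs, and t2 follows because six months is made secondary. Nor does the text say that within-group changes will be counted as success: the pairs are not restricted, but the hypothesis is framed against control.

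Finally, details of contrasts are often left to an analysis plan, and a mixed ANOVA with adjusted pairs is conventional. That does not remove the point. The article itself states its objectives, its powered test and its analysis, and the last two do not follow the ranking in the first.

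**Conclusion.** The concern holds in a limited form. The comparisons that address the primary objective are contained in the plan but not designated, and the 99% power belongs to an omnibus interaction that does not separate t2 from six months. On the protocol's own effect size, with an assumed correlation of 0.5, one Sidak-adjusted contrast against control has power of about 0.91 at 7 per arm and 0.985 at 10. That shortfall is small because the implied difference, 2.16 SD, is very large. At an assumed difference of 1 SD and 10 per arm, the same contrast has 39% power at correlation 0.5 and 64% at 0.7; the proposed analysis has 59% and 77%. The effect, SD and correlation in that second scenario are not in the documents, so those figures show direction and rough size only. The lack of a designated deciding contrast depends on none of these assumptions.

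**What to change.** State in the Data analysis section that the primary analysis is two contrasts on the primary pain outcome at t2, impact against control and cadence against control. They should be adjusted for the baseline value of that outcome, with familywise error of 5% over the two (Sidak at 0.0253 each, or Dunnett), and should not be conditional on a significant interaction. Report the six-month contrasts and impact against cadence as secondary, with 95% confidence intervals, and treat within-group changes as descriptive. In the Sample size section, say that the 99% power refers to the omnibus interaction.

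This changes wording only and uses data already to be collected. The small downside is that impact against cadence becomes formally secondary. Six months already is secondary under the stated objectives.
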